## Study design

We will conduct a community-based, cross-sectional study in which HIV prevalence will be estimated and associated with sociological, sexual and drug-using behavioral data. To obtain a representative sample of TGNB people, including hidden groups such as those who do not need medical assistance, we opted for Time Location Sampling (TLS), which takes advantage of the fact that some hard-to-reach groups tend to gather at certain (online) settings [29]. In more concrete terms, TLS approximates probability sampling by first mapping the universe of settings where TGNB people may gather and then applying a two-stage random sampling strategy. The latter involves the random selection of settings at specific time periods followed by random participant recruitment within each setting [29–31]. By applying the TLS approach, this study consists of two main parts: (i) a formative qualitative study to map social and medical settings frequented by TGNB people, which will include physical as well as digital community settings in Flanders and Brussels (Belgium) and (ii) a cross-sectional analysis to estimate HIV prevalence among Flemish TGNB people and identify associated risk factors.

After the development of the sampling frame, TGNB people will be recruited in a wide range of settings using a two-stage TLS frame for obtaining a representative sample. In this TGNB population, HIV will be screened through oral fluid samples and, at the same time, sociological, sexual and drug-using behaviors will be surveyed to reveal the association between HIV prevalence and these risk-taking behaviors. In case of a reactive oral fluid result, confirmation on a blood sample is required to allow accurate estimation of HIV prevalence. After completion of the study, we plan and report this observational study in accordance with the STROBE checklist (Strengthening the Reporting of OBservational studies in Epidemiology). Although not an interventional study, we used the relevant items of the SPIRIT checklist to report this protocol paper (S1 Checklist) and an SPIRIT overview of the schedule of assessments can be found in Fig 1.

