#### Sample size

Recent large online surveys indicated that the self-reported HIV prevalence rate in a large sample of transgender people in Europe and the US was 1.6 [15] and 2.2% [24], respectively. Since it was estimated that 30% of HIV-infected people in the European Union have not been diagnosed [38, 39], the sample size was calculated to detect an HIV prevalence rate of 3% with a precision of 1.5%. In total, 560 TGNB people need to be recruited for participation such that the expected length of the confidence interval amounts 0.03 (± 0.015) when the proportion of HIV infection is 0.03 and the level of confidence is 95% based on power test for binomial responses (RStudio, Version 3.6.1, RStudio Inc. Boston, MA, USA; Package ‘exactci’).

Because TGNB people recruited from the same cluster may share characteristics such as risk behaviors or demographics, their outcomes might be correlated. It is common to adjust for this correlation by multiplying the sample size required for a simple random sample by the “Design Effect,” also known as the “Variance Inflation Factor”. The design effect is a function of the number of individuals per cluster, m, and the intra-cluster correlation coefficient (ICC), describing the proportion of the total variation in outcomes that is due to variation between clusters.

DesignEffect=1+(m−1)ICC

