We rely on previously published ICCs for HIV outcome for the sample size calculations. However, ICCs depend on, amongst others, study’s outcome, design and population but, to date, there are no published ICCs that apply to HIV in TGNB people. We are aware of one study that used TLS in detecting HIV infection in MSM and reported ICCs (kappa-like estimator) ranging from 0.03 to 0.16 (0.08 ± 0.06) [40]. Since the mean cluster size is currently unknown, we can only estimate the design effect in advance. The cluster sizes will be fixed at multiples of ten (cfr. infra) and we expect that the proportion of small clusters will be relatively large. The average number of TGNB people sampled per cluster will hence be close to ten but the impact of the large events on the average cluster size remains to be revealed in this study. Although an average cluster size of 12 to 14 TGNB persons would be realistic based on theoretical simulations, we prefer to be conservative and to inflate the cluster size in the sample size calculations. When we for example assume on average 18 TGNB people per cluster, the design effect would be 2.36 [= (1+(18–1)*0.08] (varying between 1.51 and 3.72). Analysis of the data of the TLS involving MSM showed that the design effects may be large and that especially variation in the weights may increase the design effects [40]. To our knowledge, the importance of the design effects in the analysis of TLS data has rarely been considered. Note that the calculation of the impact of the design on the required sample size is an approximation, not only because the mean cluster size and the variability in the cluster sizes are unknown, but also since the sampling weights (cfr. infra) were not considered.

At this stage, when assuming a design effect of 2.36, 1322 TGNB people should be recruited to determine the HIV prevalence.

n=DesignEffect*560=2.36*560=1322

Finally, to assess the associated risk factors of HIV infection among TGNB people, we determined the minimum sample size for comparing two proportions in the cross-sectional study using following formula:

$$n_{Fleiss}=Design\;Effect*\frac{{\left[Z_{\alpha }\sqrt{\left(r+1)p(1-p\right)}+Z_{\beta }\sqrt{(rp_{0}(1-p_{0})+p_{1}(1-p_{1}})\right]}^{2}}{{r(p_{0}-p_{1})}^{2}}$$

$$p=\frac{p_{0}+rp_{1}}{r+1}$$

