#### Outcome of interest

An HIV diagnostic orientation test will be used to assess the presence of antibodies in an oral fluid sample as described by Platteau et al. [44] and Loos et al. [38]. The participants will receive a sampling kit identified with a unique sample code which will be linked to the anonymous behavioral questionnaire, and they will take the oral fluid aliquot following the instructions.

Oral fluid is collected and tested for the presence of HIV antibodies with the DPP HIV1/2 Assay (Chembio Diagnostic Systems, Inc). This assay has been previously evaluated at the Institute of Tropical Medicine by Beelaert et al. [45] and prequalified by WHO [46]. Samples are self-collected by the participants through swabbing of the outer gums with the DPP collecting device. The swab is placed into a sample buffer for shipment to the laboratory. Upon arrival in the lab, the swab is tested with the DPP HIV1/2 assay rapid test. The assay is based on a immunochromatographic test principle, with a test line which reacts positive in case of presence of HIV-antibodies and a control line, which allows detection of human IgG and serves as a built-in control for adequate sample quality and correct performance of the test. Prior to participation, participant registers on the website via an account. In this procedure, the participant provides both an email address and cell phone number. As soon as the result is available, participant receives an email indicating that the test result is accessible. Project collaborators monitor whether participants picked up their test result. In case a participant does not pick up a negative test result, he/she will receive two reminder emails. Participants with a reactive result who do not pick up their test result will be reminded several times via email and phone at a second stage. People with a reactive result, are followed-up for further confirmation testing on a blood sample according to standard-of-care HIV testing algorithm. Follow-up continues until project collaborators receive a confirmation test result. All initial analyses will be carried out by the Institute of Tropical Medicine (Antwerp, Belgium) and the outcome assessor will be blinded to the results of the behavioral questionnaire (risk factors). Confirmation tests will be executed at the Institute of Tropical Medicine, or via existing healthcare services.

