#### Statistical analysis plan

The proportion of HIV infection and 95% confidence interval will be estimated adjusting for clustering and unequal probability of selection. TGNB people who visited sites more frequently had a higher probability of selection in the study. (Individual) weighting factors will be calculated based on the attendance information provided by the participant to adjust for this unequal selection probability. Moreover, the probability of accepting participation and the sampling fraction (number of participants out of total number of eligible attendees at the cluster) will also be taken into account. One can expect that the real number of attendees at outreach events may deviate from the expected number used for the systematic sampling procedure. The actual number of eligible TGNB persons will always be reported in the data collection form and, if needed, weighting factors will be calculated to correct for the potential deviation in sampling probability.

Socio-demographic and geographic characteristics, sexual and drug-related risk factors of the sample will first be summarized by descriptive statistics. Logistic regression models taking into account clustering and using the sampling weights (being inversely proportional to the selection probability) will be fitted to calculate the odds ratio (OR) and 95% CI for each possible risk factor. Nine variables will be queried to map sexual risk behavior among TGNB people and three variables deal with the use of needles or risky blood contacts in the past. Depending on the number of TGNB people with HIV infection, construction of a multivariable model will be considered to estimate adjusted OR (aOR). After constructing a logistic regression model including all confounding factors (e.g. age or country of birth) that had a P<0.05 in univariate analysis, the significant risk factor(s) will then be separately added as explanatory factors to estimate aOR when deemed appropriate. Statistical analyses will be undertaken using the package ‘survey’ in RStudio to fit the above logistic regression models. Marginal models in the ‘survey’ package focus on the population mean response, averaged over all clusters, taking into account clustering and the sampling weights. Sensitivity analyses might be performed to assess the impact of e.g. potential protocol violations on the robustness of the results.

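### Confirmed HIV prevalence makes no allowance for infections the oral-fluid screen misses, so it estimates sensitivity times prevalence; the bias is small but one-directional, and a supplementary correction would show it

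*Protocol article*

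**What the plan says.** The Study design section of the protocol article ties accuracy to blood testing of reactives: "In case of a reactive oral fluid result, confirmation on a blood sample is required to allow accurate estimation of HIV prevalence". The Outcome of interest section describes the first-line test: "An HIV diagnostic orientation test will be used to assess the presence of antibodies in an oral fluid sample". Participants take the swab themselves. According to Selection and data collection procedures, people recruited in digital clusters receive the kit at home and post it back. Reactive results are followed until a blood confirmation is received. For a negative result, the only follow-up described is reminders to collect it.

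On performance, the Outcome of interest section says "This assay has been previously evaluated at the Institute of Tropical Medicine", adds that the assay is WHO-prequalified, and describes a control line that checks sample quality and test performance. No sensitivity is stated.

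The estimator is given under Statistical analysis plan: "The proportion of HIV infection and 95% confidence interval will be estimated adjusting for clustering and unequal probability of selection". That section then lists weights for attendance frequency, acceptance, sampling fraction and deviation of actual from expected attendance. The section on follow-up and missing data says that reactive swabs and confirmed status will both be analysed as outcomes. It also says that multiple imputation will be considered, a point that follows directly on the risk of missing confirmation results.

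**The concern.** Verification is one-sided. A blood test on reactives turns false positives into true negatives, but an infected participant with a non-reactive swab is counted as uninfected and no stated step reverses that. The listed adjustments deal with who was sampled and who agreed, not with how the sampled were classified. Imputation of missing confirmations does not reach these people either, because a non-reactive swab is not a missing value.

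Prevalence is a headline objective. Sampling error shrinks with recruitment, but this component does not, so neither the planned interval nor the interim sample size recalculation would reveal it. A reader of the published interval would have no means of judging how much of the reported figure depends on the swab.

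**Working it through.** **The plan's own figures.** The inputs come from the Sample size section: prevalence 0.03, half-width 0.015, 95% confidence, exact binomial interval.

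- Simple random sample: the plan states that "In total, 560 TGNB people need to be recruited for participation". The expected length of the exact (Clopper-Pearson) interval at p = 0.03 is 0.0300 at n = 560 (the first n at or below 0.03 is 561). The Wald formula gives 1.96² × 0.03 × 0.97 / 0.015² = 497, so the exact interval was used. The figure of 560 is reproduced.
- Design effect: 1 + (18 − 1) × 0.08 = 2.36, and 560 × 2.36 = 1321.6, rounded up to 1322. This is also reproduced.

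**What the confirmed proportion estimates.** Let p be true prevalence, Se and Sp the swab's sensitivity and specificity. Assume that confirmation produces no false positives and is complete or validly imputed.

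- Confirmed outcome: E = p × Se.
- Reactive-swab outcome: E = p × Se + (1 − p)(1 − Sp).

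**Size for the confirmed outcome at p = 3%.** Expected infections among 1322 are 1322 × 0.03 = 39.7. The documents give no sensitivity, so each value of Se below is an assumption.

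| Assumed Se | Expected confirmed prevalence | Shortfall (points) | Share of 1.5-point half-width | Infections missed, 39.7 × (1 − Se) |
|---|---|---|---|---|
| 0.99 | 2.97% | 0.03 | 2% | 0.4 |
| 0.95 | 2.85% | 0.15 | 10% | 2.0 |
| 0.90 | 2.70% | 0.30 | 20% | 4.0 |
| 0.80 | 2.40% | 0.60 | 40% | 7.9 |

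**Effect on the interval.** At an effective size of 560, the exact 95% interval covers the true 3% with probability 96.6% at Se = 1, 96.7% at 0.95, 96.0% at 0.90 and 92.0% at 0.80.

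**Effect of correcting.** Dividing by Se restores 3% in expectation. With Se = 0.95 treated as known, an interval of 1.5% to 4.5% becomes 1.5/0.95 = 1.58% to 4.5/0.95 = 4.74%. Keeping a 0.015 half-width on the corrected scale would take 566, 591, 625 or 705 people at Se 0.99, 0.95, 0.90 or 0.80. Multiplied by 2.36, that is 1336, 1395, 1475 or 1664. Only the last exceeds the stated budget limit of 1500.

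**The reactive-swab outcome.** With Se 0.95 and Sp 0.995: 0.0285 + 0.97 × 0.005 = 3.3%, above the truth. With Se 0.90 and Sp 0.999: 0.0270 + 0.97 × 0.001 = 2.8%, below it. The direction is not fixed.

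**The case against.** The strongest reply has four parts.

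1. The Study design sentence calls confirmation necessary for accuracy, not sufficient. A reader might infer that the plan claims confirmation also deals with missed infections; it does not say so. This stands: the sentence is incomplete rather than false, and a clarification is enough.

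2. A correction for misclassification could sit in a fuller analysis plan, and the article leaves sensitivity analyses open. This stands in part. The article does itemise the adjustments to its main estimate, none concerns test error, and the only example it gives of a sensitivity analysis is protocol violations.

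3. The size rests on an unstated sensitivity, and what the text says about the assay is favourable: prior evaluation, prequalification and a control line. This stands as a limit on the size. It does not remove the bias, since none of these makes sensitivity equal to 1.

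4. The questionnaire covers HIV testing history, so a previously diagnosed participant with a non-reactive swab might be noticed. The documents neither plan nor exclude such a check.

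Two stronger readings are tempting. One is that reported prevalence can only be understated. That applies to this error source in the confirmed outcome alone: the reactive-swab outcome can err upward, and the plan acknowledges other sources of error, such as frame coverage and refusal. The other is that the cited evaluation already supplies the correction. The text says only that an evaluation exists, not that it gives an oral-fluid sensitivity valid for self-collected, partly posted swabs.

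**Conclusion.** The point holds for the confirmed-HIV outcome. As described, the estimator targets sensitivity times prevalence, a one-directional measurement bias that recruitment does not reduce. This assumes that confirmation is free of false positives and is complete or validly imputed. If unconfirmed reactives were counted as negative, the estimate would be lower still, and dividing by sensitivity would not repair that part.

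The effect is minor over the plausible assumptions. At sensitivity of 95% or more the shortfall is at most 0.15 points, a tenth of the planned half-width, and coverage stays near nominal down to 90%. A reader might infer that the planned interval is invalid or the sample size wrong. The calculations do not support either: 560 and 1322 are reproduced, and coverage falls clearly below 95% only at the extreme assumption of 80%. This is a worthwhile refinement, not a flaw that threatens the study.

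**What to change.** Under Statistical analysis plan, add a supplementary analysis that reports the weighted confirmed prevalence divided by the oral-fluid sensitivity, with specificity set to 1 after confirmation, beside the uncorrected figure. Show it over a stated range of sensitivities. Include the value and interval from the assay evaluation cited under Outcome of interest, if that evaluation applies to self-collected oral fluid. Carry the uncertainty into the 95% interval, for example with Var(c/Se) ≈ Var(c)/Se² + c² Var(Se)/Se⁴, where c is the weighted confirmed prevalence and Var(c) its design-based variance.

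In Study design, state that blood confirmation removes false positives only and that missed infections are addressed by this supplementary analysis.

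The cost is a few lines of code and text, with no extra tests or recruitment. The downside is a slightly wider interval and reliance on an external sensitivity value, which is why the uncorrected figure should stay beside the corrected one.

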**Fig 1 pone.0266078.g001:**
[figure not shown]
Schedule of enrolment and assessments. *Because of recruitment taking place in a variety of non-research settings, a relatively short questionnaire needs to be completed at enrolment, and a follow-up questionnaire with additional questions will be sent to the participants by email (cfr. PART II).

## Methods

### Study area

We will conduct a broad survey in two out of three regions of Belgium (Flanders and Brussels). Flanders is the Dutch-speaking northern region of Belgium and counts approximately 6.6 million inhabitants in 2020. It is characterized by high land take, with many urban and rural centres. The Brussels-Capital Region is located in the central part of Belgium comprising 19 municipalities, including the City of Brussels, which is the capital of Belgium. This region has a population of around 1.2 million [32]. In total, Flanders and Brussels cover about 68% of the total Belgian inhabitants. Furthermore, large differences between the regions exist in terms of language, policies, transgender healthcare and services and the organization and structure of the TGNB community. Due to limited resources and difficulties in penetrating into the TGNB community which is to date not well sociologically mapped, TGNB people residing the French-speaking southern part of Belgium, the Walloon region, are excluded in this study. We believe that this focus will benefit the representativeness of our sample.

### Community involvement: Advisory board and peer data collectors

Throughout the study, CBPR methods will be used to ensure community involvement. CBPR entails participation of the target community throughout all phases of the research process, and is often used in research involving hard-to-reach populations. CBPR models offer mutually beneficial collaborative partnerships between those who fund, sponsor and implement research and the groups, individuals and communities affected by it [25]. Using CBPR methods, TGNB people become co-producers of knowledge [22]. In concrete terms, we will first set up a community advisory board consisting of a diverse range of TGNB people, which is strongly advised for research involving transgender people [25]. At the time of writing, the community advisory board was already composed by the researchers and consisted of 15 TGNB persons (including transgender women, transgender men, queer and non-binary persons). This advisory board will be consulted throughout several phases of the study. In first instance, the acceptability of the study within the TGNB community was already estimated by the community advisory board and we investigated how TGNB people want to be involved in studies investigating HIV in TGNB people. As a result, the community advisory board will also co-create the branding of the study, validate the community map resulting from the in-depth interviews, provide direct input on the content and comprehensibility of the questionnaires of the study, on the recruitment process and on the communication strategy of the published results. The community advisory board will not take part in outcome assessment and data analyses which will be executed by researchers who will not be involved in data collection. Consulting the community advisory board can take place online as well as offline on a regular basis, depending on the preferences of the community advisory board members, ensuring the accessibility of the setting.

Furthermore, 60% of the main research team consists of TGNB community members, and in addition three peer data collectors will support the researchers during data collection at community events and meetings during the study. Having TGNB peers involved as part of the research team appears to be a strong indicator for participants’ willingness to participate in transgender health studies [15, 22, 24]. Furthermore, peer data collectors experience fewer hurdles to overcome mistrust between researchers and hard-to-reach communities. However, the participation of TGNB people in the research team can also create a number of challenges, such as potential bias, blind spots and interpersonal factors [25]. Hence, peer data collectors require training to address challenges related to peer-to-peer research interactions, as well as to ensure all participants are treated with respect and culturally competent language is used.

### PART I: Formative community mapping study

To set up the sampling framework, a formative study is first carried out aimed at mapping community settings in which TGNB people congregate, using qualitative and ethnographic research methods. The main research questions of this formative study are: (i) how is the TGNB community in Flanders and Brussels structured, and (ii) in what settings can we recruit TGNB people in order to obtain a representative sample?

